### **Data analysis**

Data was analyzed on an intention-to-treat basis. Frequency and percentages were used to describe categorical variables, Fisher's exact test used to compare treatment groups, and logistic regression used to estimate odds ratios (ORs), and associated 95% confidence intervals (95% CIs). Means and standard deviations (SDs) were used to describe approximately normally distributed continuous data. Analysis of covariance (ANCOVA) was used to compare treatment groups at 1 years after

procedure adjusting for baseline values and to estimate mean differences between treatment groups and associated (95% CI). Medians and range (minimum, maximum values) were used to describe non-normally distributed continuous data, Wilcoxon rank sum test used to compare treatment groups and Student t test to estimate mean differences and associated (95% CI). Paired t tests were used for differences between pre- and post-measurements. For the primary outcome, we will also perform subgroup analysis based on body mass index (BMI) ( $< 24$ ,  $\geq 24$ ), history of POP procedure(primary, recurrent), or prolapse stage (stage 3, stage 4). Analyses will be performed for each subgroup in a similar way to the primary analysis. AEs will be listed and analyzed using a  $\chi$ -squared test or Fisher's exact test. Severe AEs will be listed and described in detail.

All data will be analyzed with SPSS 21.0 (IBM, Chicago, IL, USA) software packages. Statistical significance is defined as a two-sided P value of  $< 0.05$ .

## **Ethics**

This protocol and consent forms has been reviewed and approved by the central institutional review board (IRB) of Peking Union Medical College Hospital prior to the initiation of trial (JS-1278). The ethical approval was not demanded at each center. No important protocol modifications have been made after approval.

## **Data Safety and Monitoring**

the Data Safety Monitoring Board (DSMB) in our study includes two clinicians experienced in pelvic reconstructive surgery and a statistician. The members of DSMB will meet prior to the start of recruitment and at each interim meeting throughout the trial. During each meeting, they will evaluate the adherence to protocol and timeliness of recruitment. DSMB members will monitor the adverse effects, especially severe adverse events and mesh-related issues. On-site monitoring visits are planned to ensure the reliability and compliance to the protocol when needed.

A planned, masked, formal interim analysis will be performed after recruitment of half of the sample size. DSMB has the right to stop the trial ahead of schedule through voting in case of harm or benefit clearly demonstrated. Complications will be reported

in the complication registration system in China. Patients who participated will be given post-trial follow-up every year. Patients with serious complications can be transferred to the principle investigator for the management of mesh complications if needed.

## **Discussion**

This study is a continuation of our previous research. We anticipate the results of the trial will provide additional data regarding the safety and 1-3year efficacy of transvaginal mesh repair. If we are able to show self-cut mesh procedure is non-inferior to the mesh-kit procedure then it may be reasonable to recommend use of self-cut mesh due to the substantially lower cost for the patient.

## **Trial status**

The trial is ongoing. The protocol is version 1 and was completed on Jan 4th, 2018. The trial was registered on Jan 17th, 2018. The first patient was enrolled on Jan 22th, 2018. The expected date of recruitment completion will be Mar, 2020.

## **Declarations**

Ethics approval and consent to participate

The study protocol and informed consent was approved by the institutional review board of Peking Union Medical College Hospital (JS-1278) . The written informed consent will be obtained and documented for all study participants.

## **Fig.1 Study design**

[figure not shown]

| Study period |            |            |                 |
|--------------|------------|------------|-----------------|
|              | Enrollment | Allocation | Post-allocation |

| TIMEPOINTS           | -T1 | 0 | T1
(3 months) | T2
(1 years) |
|----------------------|-----|---|------------------|-----------------|
| ENROLLMENT:   |     |   |                  |                 |
| Eligibility screen   | *   |   |                  |                 |
| Informed consent     | *   |   |                  |                 |
| Allocation           |     | * |                  |                 |
| INTERVENTION: |     |   |                  |                 |
| Self-cut mesh        |     | * |                  |                 |
| Mesh-kit             |     | * |                  |                 |
| ASSESSMENTS:  |     |   |                  |                 |
| Operation time       |     | * |                  |                 |
| Blood loss           |     | * |                  |                 |
| Hospital stay        |     | * |                  |                 |
| Pain score           |     | * |                  |                 |
| Cost in admission    |     | * |                  |                 |
| POP-Q points         | *   |   | *                | *               |
| PFDI-20              | *   |   | *                | *               |
| PFIQ-7               | *   |   | *                | *               |
| PISQ-12              | *   |   | *                | *               |
| PGI-C                |     |   | *                | *               |
| Complications        |     | * | *                | *               |
| Success rate         |     |   | *                | *               |

**Fig.2.** flowchart

|      | adjusted during COVID-19 pandemic | 
1. Under the permission of national and local laws and regulations, patients are encouraged to visit the hospital for follow-up, and the research group should take care of them as much as possible. The safety of patients should be fully considered.
 
2. The 3-months follow-up after operation could be postponed as appropriate.
 
3. For patients who have reached the primary end point of 1-year after operation, if they can't visit hospital due to various reasons, they should be followed up by telephone. The survey of questionnaires will be conducted by research staff. When the situation allows, those patients would be encourage to return hospital for physical examination as soon as possible.
 
4. In case of any problem during
 |

|  |  |                                                                                                                                                                                                                    |
|--|--|--------------------------------------------------------------------------------------------------------------------------------------------------------------------------------------------------------------------|
|  |  | 
the epidemic, each center can report to PI at any time. Quality control will be conducted online. PI will supervise and check the uploaded data irregularly. The mid-term meeting will also be held online.
 |
|--|--|--------------------------------------------------------------------------------------------------------------------------------------------------------------------------------------------------------------------|

### **Original statistical analysis plan**

#### **Analysis principles**

- Analyses will be by intention-to-treat. which included all patients assigned to their randomly allocated surgery, irrespective of actual interventions undertaken.

- If there are any important imbalance in the baseline characteristics between groups, we will use logistic regression adjusting for baseline covariates for binary outcomes, and use linear regression analysis adjusting for baseline variables.
- Some important baseline characteristics will be the subject of possible subgroup analysis (see below). Whether or not the characteristics are associated with a different treatment outcome will be tested by an interaction term between the characteristic and the treatment.

### **Justification of the sample size**

The aim of the trial is to test the hypothesis that the procedure with self-cut mesh is non-inferior to the procedure with a mesh kit in terms of the composite success rate and safety. According to Fünfgeld et al.'s report, the anatomic success rate (POP-Q stage  $\geq$  II, different from this proposed study) after 12 months across all compartments was 86%. Based on a success rate of 90% in this study and 10% as the non-inferiority margin ( $\beta = 0.2$  and one-sided  $\alpha = 0.025$ ), 284 patients (142 in each group) would be required. Taking into account 10% who do not continue to the 1-year follow-up visit, a total of 316 patients will be recruited. The procedure with self-cut mesh will be considered non-inferior if the lower limit of the 95% confidence interval in success rates lies above the non-inferiority margin of -10%.

### **Interim analyses**

No interim analyses are planned in this study.

### **Statistical analysis**

#### **Characteristics of patients and baseline comparisons**

Baseline characteristics will be presented by treatment group. Frequency and percentages will be used to describe categorical variables, and means and standard deviations (SDs) or interquartile range used to describe normally distributed continuous data. We considered the independent sample test or the non-parametric Mann-Whitney test for continuous outcomes, and the  $\chi^2$  test or Fisher's exact test for categorical outcomes.

The following baseline characteristics will be presented:

- Age
- Parity
- body mass index
- smoking history
- time
- since menopause
- use of hormone replacement therapy
- medical and obstetric history,
- previous pelvic floor
- gynecological surgery

### **Description of analyses**

#### **Primary outcome**

The primary outcome measure is a composite surgical success variable measured at 1 year after surgery, defined as follows:

1. Absence of vaginal bulge symptoms as indicated by a rating of 0 on question 3 of the Pelvic Floor Distress Inventory-20 (PFDI-20): “Do you usually have a bulge or something falling out that you can see or feel in your vaginal area?”
2. No additional re-treatment (surgical or not) for POP
3. No POP-Q point at or beyond the hymen (i.e., Aa, Ba, C, Ap, Bp all < 0 cm)

All estimated difference with their 95% confidence intervals in primary outcome will be reported, the Agresti-Coull method will be used to calculate 95% CIs for differences in proportions.

#### **The secondary outcomes**

- Anatomic outcome (POP-Q score) of each vaginal segment
- Symptomatic improvement-relief of symptoms of pelvic floor disorders, including urinary, bowel and sexual function using validated instruments
- Intraoperative parameters
- Complications

- Costs, defined as the direct total charges for the surgical admission including operation, medication and use of materials (e.g., surgical mesh)

We will consider the independent sample test or the non-parametric Mann-Whitney test for continuous outcomes, and the  $\chi^2$  test or Fisher's exact test for categorical outcomes. We will use paired sample t test to compare mean continuous data within groups. For anatomic outcomes (POP-Q score) and symptomatic improvement outcomes, we will compare the changes from baseline to 1-year follow up.

### **Subgroup analyses**

For the primary outcome, we will perform subgroup analysis based on the body mass index (BMI) ( $<24$  kg/m^2 versus  $\geq 24$  kg/m^2), history of POP procedure (primary versus recurrent) or prolapse stage (stage 3 versus stage 4). Whether or not the characteristics are associated with a different treatment outcome will be tested by an interaction term between the characteristic and the treatment.

## **Final statistical analysis plan**

### **Analysis principles**

- Analyses will be by intention-to-treat, which included all patients assigned to their randomly allocated surgery, irrespective of actual interventions undertaken.
- If there are any important imbalance in the baseline characteristics between groups, we will use logistic regression adjusting for baseline covariates for binary outcomes, and use linear regression analysis adjusting for baseline variables.
- Some important baseline characteristics will be the subject of possible subgroup analysis (see below). Whether or not the characteristics are associated with a different treatment outcome will be tested by an interaction term between the characteristic and the treatment.

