### **Hypothesis**

1. The composite outcome of TVM repair using self-cut mesh will be non-inferior to the TVM repair using mesh-kit.
2. TVM repair using self-cut mesh will be non-inferior to the TVM repair using mesh-kit with respect to disease-specific quality of life, sexual function scores and complications.
3. The TVM repair using self-cut mesh will be associated with lower total hospital charges than the TVM repair using mesh-kit.

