## **Randomization**

After informed consent is signed, the patients will be registered on the web-based EDC system by a research staff to allocate each a unique study number prior to randomization. Research staff will access the system and, using the study number and initials, request randomization. Patients are randomized in a 1:1 ratio to either "self-cut mesh" group or "mesh-kit" group, according to a computer-generated randomization sequence with a block size of six. Randomization will be stratified according to centers. The patient and surgeon will be informed about the allocated operative procedure after the randomization.

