### **Description of analyses**

#### Primary outcome

The primary outcome measure is a composite surgical success variable measured at 1 year after surgery, defined as follows:

1. Absence of vaginal bulge symptoms as indicated by a rating of 0 on question 3 of the Pelvic Floor Distress Inventory-20 (PFDI-20): "Do you usually have a bulge or something falling out that you can see or feel in your vaginal area?"
2. No additional re-treatment (surgical or not) for POP
3. No POP-Q point at or beyond the hymen (i.e., Aa, Ba, C, Ap, Bp all < 0 cm)

All estimated difference with their 95% confidence intervals in primary outcome will be reported, the Agresti-Coull method will be used to calculate 95% CIs for differences in proportions.

We will apply multiple imputation techniques (five imputed datasets) for all women with missing data on primary outcome. Robustness of primary outcome will be

evaluated in sensitivity analyses performed in the ITT population without imputation. We will also conduct a secondary analysis of primary outcome based on per-protocol population, which excludes all patients who had a protocol deviation.

The secondary outcomes

- Anatomic outcome (POP-Q score) of each vaginal segment
- Symptomatic improvement-relief of symptoms of pelvic floor disorders, including urinary, bowel and sexual function using validated instruments
- Intraoperative parameters
- Complications
- Costs, defined as the direct total charges for the surgical admission including operation, medication and use of materials (e.g., surgical mesh)

We will consider the independent sample test or the non-parametric Mann-Whitney test for continuous outcomes, and the  $\chi^2$  test or Fisher's exact test for categorical outcomes. We will use paired sample t test to compare mean continuous data within groups. For anatomic outcomes (POP-Q score) and symptomatic improvement outcomes, we will compare the changes from baseline to 1-year follow up.

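### Complications are analysed only by allocated mesh; a table by mesh actually implanted should stand beside it

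*Combined protocol and SAP*

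**What the plan says.** The final SAP, under Analysis principles, states: "Analyses will be by intention-to-treat, which included all patients assigned to their randomly allocated surgery, irrespective of actual interventions undertaken". It makes no exception for safety. Under Description of analyses it lists complications among the secondary outcomes, to be compared by a chi-squared or Fisher's exact test, again with no population named.

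The final SAP has one other set, and it is tied to a single outcome: "We will also conduct a secondary analysis of primary outcome based on per-protocol population, which excludes all patients who had a protocol deviation".

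The current protocol (edition dated March 4, 2019) agrees. Its Data analysis section says "Data was analyzed on an intention-to-treat basis". It gives adverse events no set of their own and adds that "Severe AEs will be listed and described in detail".

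Safety is part of what the trial claims. Hypothesis 2 says that self-cut repair will be "non-inferior to the TVM repair using mesh-kit with respect to disease-specific quality of life, sexual function scores and complications", and the SAP's sample size section includes safety in the non-inferiority aim.

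**The concern.** Mesh exposure is a harm of the device in the body. Suppose a woman allocated to the kit receives self-cut mesh and later has an exposure. Under the stated rule the event is reported as a kit complication, and the reverse holds for a switch the other way. Once any such switch occurs, neither reported rate is the rate among women who received that mesh, and the contrast between arms shrinks. For a claim of no worse safety, a shrunken contrast is not conservative when the new procedure is truly worse.

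The design makes switching plausible. "The patient and surgeon will be informed about the allocated operative procedure after the randomization" (Randomization). Women pay for the implant themselves and know the price difference (Study design). Every surgeon is expected to be able to perform both operations (Participating hospitals). Women may withdraw at any time (Study population and recruitment), so one who withdraws before surgery would count in the denominator without being at risk from a mesh.

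**Working it through.** **The plan's own figure.** The documents give no figure for crossover, for non-implantation or for a margin on complications. The only related calculation is the sample size, which reproduces: (1.960 + 0.842)² × (0.9×0.1 + 0.9×0.1) / 0.10² = 141.3, so 142 per group and 284 in total; 284 / 0.9 = 315.6, so 316 as in the SAP. Nothing below changes it.

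**Inputs.**
- 6.9%: exposure or erosion with self-cut mesh (protocol, Background). This is an earlier series with uncoated mesh.
- 10.5% (30/286): erosion with the titanium-coated kit (protocol, Background). Median follow-up was 36 months.
- The two cohorts are not comparable, so the figures only set a scale. The 8.9% in the same section is mesh-related complications, not exposure, and is not used.
- c, the share in each arm receiving the other mesh: assumed 0 to 10%.
- u, the share in each arm never implanted: assumed 0 to 5%, with no mesh risk.

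**Formula.** With per-device risks pS (self-cut) and pK (kit):
- self-cut arm as reported = (1 − c − u)·pS + c·pK
- kit arm as reported = (1 − c − u)·pK + c·pS
- reported difference = (1 − 2c − u)·(pS − pK)

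**Results for a true difference of 10.5 − 6.9 = 3.6 points, in either direction.**
- c = 0, u = 0: 1.00 × 3.6 = 3.6 points. With full adherence there is no effect.
- c = 2%, u = 2%: 0.94 × 3.6 = 3.4 points.
- c = 5%, u = 0: 0.90 × 3.6 = 3.2 points. At 158 recruited per arm this is about 8 women switching in each arm (0.05 × 158 = 7.9).
- c = 10%, u = 5%: 0.75 × 3.6 = 2.7 points.
- Switching one way only, with 5% of the kit arm receiving self-cut mesh and u = 0: 0.95 × 3.6 = 3.4 points.

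**Unequal non-implantation.** The formula assumes the same u in both arms. If 5% are never implanted only in the arm with the higher risk, the difference is 10.5×0.95 − 6.9 = 3.1 points. If only in the arm with the lower risk, it is 10.5 − 6.9×0.95 = 3.9 points. Non-implantation in one arm can thus narrow or widen the difference.

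**Compared with sampling error.** At 10.5% and 6.9% with 142 per arm, the half-width of the 95% confidence interval is 1.96 × √[(0.105×0.895 + 0.069×0.931)/142] = 6.5 points. The shifts above are at most 0.9 points.

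**The case against.** By-allocation reporting is a legitimate comparison and the only one that randomisation protects. Adverse events will also be listed and severe ones described, which gives some view of individual cases. Both points stand, and they are why the by-allocation table should stay. Neither yields a rate for each mesh among the women who received it.

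A reader might infer that intention-to-treat is the only set in the SAP. It is not: the final SAP adds a per-protocol set, though only for the primary outcome ("We will also conduct a secondary analysis of primary outcome based on per-protocol population").

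A reader might also infer that harms are in fact credited to the wrong device and that unimplanted women dilute the rates. The documents do not show this. They report no crossover. The current protocol, in the pandemic paragraph under Data collection, says enrolment was complete and all patients had had surgery. That weakens the never-implanted part considerably, although it does not say which mesh each woman received.

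Finally, a reader might infer that the rule always helps self-cut mesh. It does so only if self-cut is truly worse. The background figures, for what they are worth, have self-cut lower (6.9% against 10.5%), and the investigators' own 18 titanium-mesh patients had no exposure. If that direction is right, counting by allocation works against self-cut mesh.

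**Conclusion.** The gap is real and of low severity. Allocation is the only basis on which the final SAP analyses complications, whatever mesh was implanted, and the protocol makes a non-inferiority claim "with respect to disease-specific quality of life, sexual function scores and complications". If women switch mesh, the two complication rates move together; which procedure gains depends on which is truly worse.

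The size rests entirely on assumed departures. It is nil with full adherence and about 0.4 points on an illustrative 3.6-point difference at 5% crossover each way. It reaches 0.9 points only at 10% crossover each way with 5% never implanted. This is a weakness in specification, not a demonstrated bias, and it does not touch the analysis set for the primary outcome.

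**What to change.** In the final SAP, under the secondary outcomes:

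- Keep the by-allocation table of complications.
- Add a safety set: all women who had the study operation, grouped by the mesh actually implanted. Report perioperative complications (Clavien-Dindo) and mesh-related complications (IUGA/ICS coding) in it, with rates, risk difference and 95% confidence interval.
- Report by arm how many women received the other mesh and how many received no implant.
- Confirm that the mesh implanted is captured. The protocol's Data collection section does not list it, although material fees are recorded.

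No decision rule linking the two tables is proposed. The plan sets no margin for complications, so agreement between the tables would have no defined meaning.

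The cost is a few lines of SAP text and one extra set of tables, with no change to sample size or conduct provided the mesh field exists. The downside is that the comparison by mesh implanted is not protected by randomisation, so it supplements the by-allocation table and does not replace it.

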### **Justification of the sample size**

The aim of the trial is to test the hypothesis that the procedure with self-cut mesh is non-inferior to the procedure with a mesh kit in terms of the composite success rate and safety. According to Fünfgeld et al.'s report, the anatomic success rate (POP-Q stage  $\geq$  II, different from this proposed study) after 12 months across all compartments was 86%. Based on a success rate of 90% in this study and 10% as the non-inferiority margin ( $\beta = 0.2$  and one-sided  $\alpha = 0.025$ ), 284 patients (142 in each group) would be required. Taking into account 10% who do not continue to the 1-year follow-up visit, a total of 316 patients will be recruited. The procedure with self-cut mesh will be considered non-inferior if the lower limit of the 95% confidence interval in success rates lies above the non-inferiority margin of -10%. The enrollment will be more than 10 patients in each center.

